# Dual thrombolytic therapy with mutant pro-urokinase and small bolus alteplase for ischemic stroke (DUMAS): study protocol for a multicenter randomized controlled phase II trial

**DOI:** 10.1186/s13063-022-06596-z

**Published:** 2022-08-09

**Keywords:** Thrombolytic treatment, Mutant pro-urokinase, Alteplase, Ischemic stroke, Randomized controlled trial

## Abstract

**Background:**

The effectiveness of alteplase for ischemic stroke treatment is limited, partly due to the occurrence of intracranial and extracranial hemorrhage. Mutant pro-urokinase (m-proUK) does not deplete fibrinogen and lyses fibrin only after induction with alteplase. Therefore, this treatment has the potential to be safer and more efficacious than treatment with alteplase alone. The aim of this study is to assess the safety and efficacy of thrombolytic treatment consisting of a small bolus alteplase followed by m-proUK compared with standard thrombolytic treatment with alteplase in patients presenting with ischemic stroke.

**Methods:**

DUMAS is a multicenter, phase II trial with a prospective randomized open-label blinded end-point (PROBE) design, and an adaptive design for dose optimization. Patients with ischemic stroke, who meet the criteria for treatment with intravenous (IV) alteplase can be included. Patients eligible for endovascular thrombectomy are excluded. Patients are randomly assigned (1:1) to receive a bolus of IV alteplase (5mg) followed by a continuous IV infusion of m-proUK (40 mg/h during 60 min) or usual care with alteplase (0.9 mg/kg). Depending on the results of interim analyses, the dose of m-proUK may be revised to a lower dose (30 mg/h during 60 min) or a higher dose (50 mg/h during 60 min). We aim to include 200 patients with a final diagnosis of ischemic stroke. The primary outcome is any post-intervention intracranial hemorrhage (ICH) on neuroimaging at 24 h according to the Heidelberg Bleeding Classification, analyzed with binary logistic regression. Efficacy outcomes include stroke severity measured with the National Institutes of Health Stroke Scale (NIHSS) at 24 h and 5–7 days, score on the modified Rankin scale (mRS) assessed at 30 days, change (pre-treatment vs. post-treatment) in abnormal perfusion volume, and blood biomarkers of thrombolysis at 24 h. Secondary safety endpoints include symptomatic intracranial hemorrhage, death, and major extracranial hemorrhage. This trial will use a deferred consent procedure.

**Discussion:**

When dual thrombolytic therapy with a small bolus alteplase and m-proUK shows the anticipated effect on the outcome, this will lead to a 13% absolute reduction in the occurrence of ICH in patients with ischemic stroke.

**Trial registration:**

NL7409 (November 26, 2018)/NCT04256473 (February 5, 2020)

**Supplementary Information:**

The online version contains supplementary material available at 10.1186/s13063-022-06596-z.

## Background

Currently, recombinant tissue plasminogen activator alteplase is the only FDA-approved agent for the thrombolytic treatment of ischemic stroke. This thrombolytic treatment with alteplase in patients with ischemic stroke leads on average to improved reperfusion in about 30% of patients and increases the likelihood of a good clinical outcome in one of every ten treated patients [1]. Apart from its limited efficacy, it carries a risk of symptomatic intracranial hemorrhage of 6-7% [2].

Treatment with endovascular thrombectomy is effective in patients with ischemic stroke due to a large-vessel occlusion in the anterior circulation [3], which is present in at most 30% of ischemic stroke patients presenting at the emergency department [4, 5]. For patients with ischemic stroke without a large-vessel occlusion, reperfusion can only be reached through thrombolytic treatment [6]. There is a need for a better and safer thrombolytic therapy, which expands the number of patients that can be treated safely and successfully. Preclinical and clinical studies have indicated that dual thrombolytic therapy, mimicking the physiological design of thrombolysis, with small bolus alteplase followed by a mutant pro-urokinase (m-proUK) has a significant potential to be safer and more efficacious than the FDA-approved regimen of standard dose alteplase alone (0.9 mg/kg) [7–10]. M-proUK is a single-point mutation of the single-chain zymogen plasminogen activator, pro-urokinase, with less susceptibility to non-specific activation into its enzymatic, two-chain form, urokinase [9]. Moreover, m-proUK by itself does not lyse hemostatic fibrin, only partially degraded fibrin [8, 11]. When the low dose alteplase is cleared from the systemic circulation, m-proUK will only induce intravascular clot lysis, and spare hemostatic fibrin. Therefore, this therapeutic regimen has the potential to be safer and more efficacious than treatment with alteplase [7–9].

### Objectives

To assess the safety of treatment with a dual plasminogen activator (in short: thrombolytic), which consists of a small bolus of intravenous (IV) alteplase followed by IV infusion of m-proUK against usual treatment with IV alteplase in patients presenting with ischemic stroke.To assess the preliminary efficacy of treatment with a dual plasminogen activator, which consists of a small bolus of IV alteplase followed by IV infusion of m-proUK against usual treatment with IV alteplase in patients presenting with ischemic stroke.

## Methods

### Study design

The DUal thrombolytic treatment with Mutant pro-urokinase and small bolus Alteplase for ischemic Stroke (DUMAS) trial is a multicenter, phase II trial with a prospective randomized open-label blinded end-point (PROBE) design and an adaptive design for dose optimization (Fig. 1). Thrombolytic treatment consisting of a small bolus of IV alteplase and IV m-proUK will be compared with usual thrombolytic treatment with alteplase 0.9 mg/kg. An overview of the main study procedures is provided in Fig. 2. Because the exact optimal dose of IV m-proUK for patients with ischemic stroke is still unknown, sequential interim analyses will be performed allowing adaptation of the IV m-proUK dose. A detailed description of this adaptive design can be found in Supplemental File 1. The “Standard Protocol Items: Recommendations for Interventional Trials” (SPIRIT) checklist is provided as Supplemental File 2 [12]. The study will run in several hospitals in the Netherlands.

**Fig. 1 Fig1:**
[figure not shown]
Trial logo

**Fig. 2 Fig2:**
[figure not shown]
SPIRIT figure. mRS indicates modified Rankin scale; NIHSS, National Institutes of Health Stroke Scale; SAE, serious adverse events. *t_−1_: directly before randomization, t_0_: randomization, t_1_ = directly after randomization; t_2_ = at 1 h; t_3_ = at 3 h; t_4_ = at 24 h; t_5_ = at 5–7 days or at discharge if earlier; t_6_ = at 30 days. **Informed consent: as early as deemed possible after IV thrombolysis. ***Administration of IV thrombolytic therapy directly after randomization. ****Neuro-imaging at baseline consists of non-contrast CT, CT-perfusion, and CT-angiography or brain MRI and MRA. Neuro-imaging at 24 h consists preferably of a brain MRI

### Patient population

The study population will be drawn from patients with a clinical diagnosis of ischemic stroke at the Emergency Department.

Patients are eligible for inclusion in DUMAS when they are 18 years or older and have a clinical diagnosis of ischemic stroke with a deficit on the National Institutes of Health Stroke Scale (NIHSS) of at least 1 point. Non-contrast computed tomography (NCCT) or magnetic resonance imaging (MRI) should rule out intracranial hemorrhage (ICH) and patients should meet the criteria for standard treatment with IV alteplase according to national guidelines [13]. Treatment should therefore be possible within 4.5 h from symptom onset or last seen well or between 4.5 and 12 h from symptom onset or last seen well, if the infarct core is less than 25 mL and the penumbra is at least the same size as the infarct core (i.e., total ischemic volume/infarct core mismatch ≥ 2.0) [14], or in case of lacunar syndrome [15], if there is a diffusion-weighted imaging (DWI) and fluid attenuation inversion recovery (FLAIR) mismatch, consistent with Dutch national guidelines for stroke [16].

Exclusion criteria are eligibility for endovascular thrombectomy (i.e., patients with a proximal large artery occlusion on CT angiography or magnetic resonance angiography), contra-indication for treatment with IV alteplase according to national guidelines, pre-stroke modified Rankin Scale (mRS) score > 2, known pregnancy, contra-indication for MRI, and participation in any therapeutic trial other than DUMAS.

There are no dropout criteria.

### Randomization

#### Sequence generation

Patients will be randomized 1:1 to standard thrombolytic treatment with alteplase alone vs. dual thrombolytic treatment with a bolus alteplase and m-proUK. The randomization procedure will be web-based, using permuted blocks. Randomization will be stratified for the center. The allocation sequence was generated by the independent trial statistician.

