### Statistical analyses

Baseline data by treatment allocation will be reported with standard statistical procedures and missing values will be reported. For regression analyses, missing values, except the primary outcome, will be imputed using multiple imputation (*n*=5). We will perform and report 4 analyses, of which the first is the primary:Simple modified intention-to-treat analysis to assess overall safety and efficacy. This is a modified intention-to-treat analysis because we exclude patients who did not give consent to participate in the study. We will additionally report safety parameters based on the full cohort, including patients who did not give consent.Targeted modified intention-to-treat analysis excluding patients with a final diagnosis other than ischemic stroke to assess safety and efficacy in the target population.Targeted modified on-treatment analysis to assess the safety and efficacy in patients who actually received treatment excluding patients with a final diagnosis other than ischemic stroke.Per-protocol analysis.

Additionally, we will perform subgroup analyses on categorized baseline variables including age, sex, systolic blood pressure, ASPECTS, time from onset to study treatment, NIHSS score, extracranial carotid or vertebral arterial occlusion, pre-study antiplatelet treatment, DWI lesion (yes/no), and lacunar syndrome (yes/no). Subgroup analyses will be done by testing for interaction of the subgroup indicator with treatment.

The effect of the study treatment on the primary outcome will be assessed with multivariable logistic regression with study treatment as a binary independent variable (m-proUK vs. control). Adjusted and unadjusted effect estimates with corresponding 95% confidence interval (CI) will be reported. The effect estimate will be adjusted for important prognostic factors at baseline, which include at least age and time from onset of symptoms to randomization. Stroke severity (NIHSS score), lacunar syndrome (yes/no) [11], systolic blood pressure, antiplatelet treatment, and endovascular treatment (yes/no) will be considered additionally in this order. Whether the dosing (initial vs. modified) of the study treatment modifies the treatment effect, will be analyzed with a multiplicative interaction parameter in the main analysis.

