### Sample size

We will include 200 patients with a final diagnosis of ischemic stroke randomized 1:1 to either standard thrombolytic treatment or dual thrombolytic treatment. We assume that the primary outcome, any ICH, will occur with a probability of 20% with standard thrombolytic treatment and a probability of 7% in the patients treated with dual thrombolytic therapy [24]. This leads to an overall effect (odds ratio (OR)) of 0.3. This sample size will provide us with a power of at least 77% to detect a statistically significant effect on the primary outcome. This estimate does not take into account the use of multivariable adjustment for differences in baseline characteristics in the primary analysis.

To ensure sufficient power in the targeted modified on-treatment analysis, an additional patient will be randomized and included (i.e., replaced) for each patient whodid not give consent for participation in the study, orfor any reason did not receive the full dose of thrombolytics as assigned, orhad a final diagnosis other than ischemic stroke (i.e., stroke mimic).◦ We estimate that up to 20% of the included patients will not have a final diagnosis of ischemic stroke [25].

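### Randomization is stratified by center, but the covariates named for the primary model do not include center; if bleeding risk differs by center, a little power is lost

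*Protocol article*

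**What the plan says.** **Design.** The article's Sequence generation section describes 1:1 web-based randomization in permuted blocks and adds: "Randomization will be stratified for the center". Center is the only stratification factor named. The number of centers is not given; Study design says only "The study will run in several hospitals in the Netherlands".

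**Analysis.** Statistical analyses specifies logistic regression with treatment as a binary term, adjusted for "important prognostic factors at baseline, which include at least age and time from onset of symptoms to randomization". Stroke severity and lacunar syndrome head a second list, which ends: "systolic blood pressure, antiplatelet treatment, and endovascular treatment (yes/no) will be considered additionally in this order". That makes two mandatory covariates and five candidates. Neither list contains center, and no random effect, center-stratified test or reason for leaving center out is given. The section ends by pointing to a statistical analysis plan on the trial website, which is not at hand.

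**Size.** The Sample size section plans 200 patients, 20% vs 7% with any intracranial hemorrhage, an odds ratio of 0.3 and power of at least 77%. It says that this figure ignores covariate adjustment.

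**The concern.** Blocking within center balances the arms on center. If center predicts bleeding, differences between centers largely cancel out of the treatment comparison. A crude analysis still counts those differences as noise in its standard error. Its test is then conservative, and some of what stratification bought is not used.

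The article does not merely leave adjustment to another document. It publishes the mandatory covariates and ranks the optional ones, and the one factor used in randomization is not among them. At stake is a small amount of power in a trial planned at only 77%.

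**Working it through.** **1. The plan's own power figure.** Inputs from Sample size: 100 per arm, 20% vs 7%. Two-sided 5% is assumed, since only 95% intervals are mentioned.

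- Pooled rate: (0.20 + 0.07)/2 = 0.135.
- SE under the null: √(2 × 0.135 × 0.865/100) = 0.0483.
- SE under the alternative: √(0.20 × 0.80/100 + 0.07 × 0.93/100) = 0.0474.
- Power: Φ[(0.13 − 1.96 × 0.0483)/0.0474] = 77.1%. The stated 77% is reproduced.
- Odds ratio: (0.07/0.93)/(0.20/0.80) = 0.301.
- Expected events: 100 × 0.20 + 100 × 0.07 = 27.

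**2. Direction and rough size by hand.** Let σ be the between-center SD on the logit scale and take a 20% risk in both arms. The between-center variance is about [0.20 × 0.80 × σ]². For σ = 0.5 this is 0.08² = 0.0064, or 0.0064/0.16 = 4% of the outcome variance. Blocking removes most of that share from the arm difference, but the crude SE keeps it. The SE is therefore about 1/√0.96 = 1.02 times too large, and the true type I error is about 2Φ(−1.96/√0.96) = 4.5%. For σ = 1.0 the share is 16% and the same formula gives 3.2%; it is rough at that spread.

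**3. Simulation.** Assumed: 200 patients, blocks of 4, 5 or 10 centers of unequal size, normal center effects, overall rates held at 20%/7% (power) or 20%/20% (null), 3,000 runs per cell. The simulation SE is about 0.7 to 0.8 points for power and 0.3 to 0.4 for type I error. Differences within a row are more precise, because all tests used the same simulated data. CMH is the Cochran-Mantel-Haenszel test stratified by center.

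Power, %:

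| Centers | σ | Score, no center | CMH by center | Logistic Wald, no center | Logistic Wald, fixed centers |
|---|---|---|---|---|---|
| 5 | 0 | 79.4 | 79.3 | 77.4 | 78.4 |
| 5 | 0.5 | 79.5 | 79.7 | 77.3 | 78.6 |
| 5 | 1.0 | 78.4 | 80.7 | 74.8 | 78.6 |
| 5 | 1.5 | 76.7 | 80.4 | 70.9 | 75.4 |
| 10 | 0 | 80.0 | 79.7 | 78.2 | 79.8 |
| 10 | 0.5 | 79.2 | 79.3 | 77.5 | 79.5 |
| 10 | 1.0 | 79.5 | 81.3 | 76.5 | 80.5 |
| 10 | 1.5 | 77.7 | 82.3 | 73.2 | 80.1 |

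Type I error of the score test without center was 4.5–4.7% at σ = 0.5, 3.7–4.0% at σ = 1.0 and 2.5–3.2% at σ = 1.5. CMH by center stayed at 4.4–5.4% throughout.

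The logistic columns overstate the gain. They already differ by 1.0 and 1.6 points at σ = 0, where there is nothing to recover, and with 10 centers and σ = 0 the fixed-center test had a type I error of 6.0%.

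**4. Two further simulations**, each with 10 assumed unequal centers, score test without center vs CMH:

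- With sizes from 60 down to 4 and 8,000 runs: 79.7% vs 79.3% at σ = 0, 77.7% vs 78.1% at 0.5, 74.5% vs 75.8% at 0.8 and 71.6% vs 73.9% at 1.0.
- In the other: 78.0% vs 77.7%, 78.7% vs 79.1% and 77.8% vs 79.5% at σ = 0, 0.5 and 1.0. The score test's type I error was about 4.3% at σ = 1.0. A likelihood-ratio test from a random-intercept model ran at 5.5–6.4%.

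Power levels differ between simulations because the set-ups differ. The differences within each agree.

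**5. What these spreads mean.** Around a typical-center risk of 20% (logit −1.386), the middle 95% of centers spans −1.386 ± 1.96σ on the logit scale: about 9% to 40% for σ = 0.5, 3% to 64% for σ = 1.0 and 1% to 83% for σ = 1.5.

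**6. Room in the model.** Treatment, two mandatory and five candidate covariates make at least 8 coefficients: 27/8 = 3.4 events each. Nine indicators for 10 centers would bring this to 27/17 = 1.6.

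**The case against.** **Center may already be in the plan.** A reader might infer that the stratification is definitely ignored. The article does not support that. Its covariate list is a minimum, and how center enters a model is usual content for an analysis plan, which is not shown here. What stands is narrower: the article chose to list and rank covariates, and the stratification factor is not among them.

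**The effect is small.** At σ = 0.5, the gain from score test to CMH (0.1 to 0.4 points) is about as large as the loss when centers do not differ (0.1 to 0.4 points). This stands, and it sets the weight of the point.

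**Large spread is doubtful.** Eligibility follows national guidelines, thrombectomy candidates are excluded, 24 h MRI is standard, and two blinded core-laboratory readers assess the outcome. All of this argues against risks running from 3% to 64% across centers. CT replaces MRI only for contraindications, so follow-up practice is weak evidence for center differences. This stands too.

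**The simulated tests are not the planned one.** Covariates were not simulated and could absorb part of any center difference. This limits precision, not direction.

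**The interval would not simply narrow.** A reader might infer that adding center gives a tighter interval for the odds ratio. In logistic regression, a prognostic term generally does not narrow the interval for the log odds ratio. The gain comes mainly from the conditional odds ratio lying further from 1, and that is a different quantity from the crude one.

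**Conclusion.** The point holds as a minor matter of efficiency and of consistency between design and analysis. Center stratifies the randomization and is missing from the adjustment terms that the article names.

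If bleeding risk differs by center, leaving center out costs about 0 to 2 points of power for modest spread. It costs a few points only for large spread: 3.7 to 4.6 at σ = 1.5 by score test vs CMH, and up to 6.9 on the logistic comparison, which overstates it. These sizes rest on an assumed number and size of centers, block size and spread, and on 200 patients at 20% vs 7%.

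A reader might go further and infer that the primary result would be biased or its false-positive risk raised. Neither follows. The error is conservative, and blocking keeps the arms balanced on center whether or not the model includes it.

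**What to change.** Recruitment is reported as complete, so the change is one of analysis wording, to be made before outcomes are joined to allocation (if the analysis plan does not already say it):

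- Name center among the always-included terms of the primary model, with very small centers pooled by a rule fixed in advance. Use a random intercept or a stratification term, not one indicator per center, because only about 27 events are expected.
- Report a center-stratified Mantel-Haenszel odds ratio as the otherwise unadjusted estimate.
- State that the adjusted odds ratio is conditional on center.
- Check the small-sample type I error of the random-intercept test before adopting it, given the 5.5–6.4% seen in one simulation.

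If center is left out on purpose, a sentence giving the reason would also settle the point.

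The cost is a few lines of text, one model term and that check. If centers do not differ, the loss is at most a few tenths of a point of power (0.1 to 0.4 in the simulations). No new data are needed.

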#### Allocation concealment mechanism

The allocation sequence was unknown to all investigators.

#### Implementation

Patients will be randomized by the treating physician.

### Blinding

Clinical outcomes, such as NIHSS scores and serious adverse events are collected by trained research personnel. Standardized telephone interviews to assess the mRS score at 1 month will be conducted from a central location by experienced research nurses, unaware of treatment allocation [17, 18]. They will instruct patients or relatives before starting the interview not to say anything about the performed procedure or the admission in the hospital. Neuroimaging will be assessed by an imaging core laboratory blinded to study treatment allocation. Members of the imaging core laboratory are unaware of clinical data including treatment allocation, but were informed about baseline clinical symptoms. Clinical symptoms were defined as side of the hemiparesis, presence of aphasia, or non-localizing symptoms for the patients without hemiparesis or aphasia. Follow-up neuroimaging on which the primary outcome is determined will be assessed by two independent members of the imaging core laboratory. If the two imaging core laboratory assessments do not match, disagreements will be resolved by consensus. Outcome data will be entered in a database that is kept separated from the main clinical database, which includes information about the treatment allocation.

### Study treatment

The intervention arm will receive a small bolus of IV alteplase 5 mg, which will be followed by a continuous infusion of m-proUK, either 40 mg in 60 min (initial dose) or an alternate dose, independent of patient weight. Depending on the result of interim analyses, the m-proUK dosage may be revised to:Higher than the initial dose, by 25% (i.e., 50 mg in 60 min)Lower than the initial dose, by 25% (i.e., 30 mg in 60 min)

A detailed description of this adaptive design for dose optimization can be found in Supplemental File 1. In case of a dose change, only one switch back to the original dose is allowed without further changes to the dose. The total number of different dosages used in the trial will therefore not exceed two, in order to retain sufficient precision in the estimate of dose-related treatment effect.

The control arm will receive standard treatment with IV alteplase alone in a dose of 0.9 mg/kg (10% bolus + 90% infusion in 60 min), maximum dose 90 mg.

